### Power Calculation

Based on previous literature, a minimum sample size of 20 participants has been identified as appropriate for a pilot study to provide preliminary estimates of variability and to evaluate key feasibility parameters. These estimates are informed by existing caregiver pilot study interventions [24,25]. To account for expected attrition, a total sample size of 30 participants will be recruited. This target provides a buffer to maintain the minimum sample needed to evaluate feasibility outcomes and to estimate variance for future sample size calculations, while accounting for potential data loss due to loss to follow-up.

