### Progression Criteria

We prespecified quantitative and qualitative progression criteria to guide decisions about whether to proceed to a future definitive trial. Key thresholds are recruitment success 80% or higher (≥24/30 participants) of the target, amend-and-reassess if 50% to 79% (15-23/30) are enrolled, and stop or redesign if less than 50% (<15 participants) are enrolled. Retention success is 80% or higher completion of both postintervention and 1-month follow-up assessments, amend if 60% to 79% (18-23/30) complete, and stop if less than 60% (<18 participants). Intervention adherence success is 75% or more of the participants (≥23/30 participants) completing at least 2 of 3 scenarios and reviewing virtual clinician feedback during the loan period, amend if 50% to 74% (15-22/30), and stop if less than 50% (<15 participants). Data completeness success is 90% or higher (≥27/30) at baseline and 80% or higher (≥24/30) at post-intervention and 1-month follow-up for primary caregiver measures; amend for baseline 75% to 89% (≥23/30) or post-intervention or 1-month 60% to 79% (18-23/30). Safety or tolerability success is 15% or lower (<4 participants) reporting moderate or severe simulator sickness or adverse events attributable to device or software and no serious adverse events, amend if 16% to ‐30% (5-9/30) report moderate symptoms that are remediable, or stop if more than 30% (>9 out of 30 participants) report moderate or severe symptoms or any serious adverse event attributable to the intervention. Acceptability success is 70% or higher (≥21/30 participants) reporting willingness to use the MVP again or recommend it, amend if 50% to 69% (15-21/30), or stop if less than 50% (<15/30). Qualitative signals from interviews, reflection notes, and field notes will be used alongside these thresholds to interpret feasibility. Decision rules are to proceed to a definitive trial without substantive changes if most key criteria meet success thresholds, proceed with specified protocol modifications if criteria fall in the amend range but no major safety signals exist, and stop and redesign if multiple key criteria fall in the stop range or qualitative data reveal fundamental, unresolvable concerns. All progression decisions will be reported and justified in the Results section, and the CONSORT pilot flow diagram will present numbers screened, enrolled, completed at each time point, and the reasons for nonparticipation or dropout.

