### Outcome Measures

The primary focus of this pilot is feasibility. Feasibility outcomes that will be reported include recruitment and enrollment rates, consent rate, retention and follow-up rates, adherence to the intervention (eg, time spent in scenarios and number of scenarios completed), data completeness, and adverse events or dropouts related to tolerability. Acceptability and usability outcomes will be assessed through participant responses and standardized instruments. Caregiver outcomes are collected as exploratory measures to describe change over time and to estimate variability for future studies. These caregiver outcome measures, completed at the 3 time points where indicated (Table 1), include:

Caregiver competence: Caregiver Competence Scale [26], a 4-item scale assessing perceptions of ability to manage caregiving tasks effectively.Resilience: Connor-Davidson Resilience Scale [27], a 10-item self-report questionnaire assessing ability to cope with adversity.Empathy: Empathy Assessment Scale [28], a 13-item scale evaluating cognitive and affective components relevant to caregiving.Stress: Perceived Stress Scale [29], a 10-item scale measuring perceived stress.Secondary exploratory measures include behavioral disturbances in people living with dementia (Neuropsychiatric Inventory) [30], depressive symptoms (Center for Epidemiologic Studies Depression Scale) [31], caregiver burden (the Burden Questionnaire) [32], and quality of life (Adult Carer Quality of Life Questionnaire) [33].

VR-SIM Carers is also being evaluated for its feasibility, acceptability, and tolerability on caregiver outcomes, and these will be assessed at multiple points. For technical feasibility, participants will be asked about their ability to carry out the study workflow and the amount of time they engaged with the VR scenarios. Recruitment and retention will be tracked to inform feasibility. For acceptability, participants will be asked about willingness to use the MVP on the expression of interest form and consent form. For tolerability, participants will be asked about any side effects related to hardware or software at the week 1 phone check-in, and the number of dropouts due to adverse events will be tracked.

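### Safety progression is judged by a ceiling on the number reporting symptoms, with counts fixed to 30, so missing side-effect reports can only help it pass

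*Protocol article*

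**What the plan says.** Progression Criteria gives three safety bands.

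- Success: "Safety or tolerability success is 15% or lower (<4 participants) reporting moderate or severe simulator sickness or adverse events attributable to device or software", together with no serious adverse events.
- Amend: 16% to 30%, printed as "5-9/30) report moderate symptoms that are remediable".
- Stop: "stop if more than 30% (>9 out of 30 participants) report moderate or severe symptoms", or any serious adverse event attributable to the intervention.

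The criteria for recruitment, retention, adherence, data completeness and acceptability each require at least a given number to do something. Safety alone sets a maximum.

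Side-effect information comes from a few places. Textbox 1 lists the Simulator Sickness Questionnaire at the week 1 orientation only, and Table 1 does not list it. Outcome Measures adds: "For tolerability, participants will be asked about any side effects related to hardware or software at the week 1 phone check-in". Textbox 1 puts that call in weeks 2 and 3, so the two places must be reconciled. Outcome Measures also tracks dropouts due to adverse events. Interviews, check-in notes, reflection notes and 1-month open text are analysed qualitatively for tolerability.

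Losses are expected. Power Calculation says: "To account for expected attrition, a total sample size of 30 participants will be recruited". The paragraph after Table 1 says that attrition is reported as a feasibility outcome and that quantitative analyses mainly use available cases. It does not mention the progression counts, and Progression Criteria does not refer back to it.

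**The concern.** Under a floor, missing data works against the program. Under a ceiling on reports with a fixed count, it works in the program's favour. A participant who has worn the headset, then leaves without giving a reason or cannot be reached, adds nothing to the number reporting but still has a place among the 30. People who stop using a headset quietly may include some who tolerated it badly, so the gap may not be neutral.

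Safety is one of six criteria behind the decision to go on to a definitive trial, and the rule is to proceed unchanged if most are met. Suppose attrition puts retention and data completeness in the amend band and the other three non-safety criteria succeed. A safety success then makes four of six, whereas a safety amend leaves three of six.

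**Working it through.** **1. The printed counts.** 15% of 30 is 4.5, so the percentage allows 4 reporters (4/30 = 13.3%), while the printed count allows 3 (3/30 = 10.0%). The success count therefore does not reproduce its percentage, and 4 reporters fall in no count band. This is a separate inconsistency that must be reconciled. The amend count (5/30 = 16.7% to 9/30 = 30.0%) and the stop count (10/30 = 33.3% upward) do match their percentages.

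**2. Direction.** Let m be the number of the 30 who give a side-effect report and X the number of those reporting a qualifying event. The rule compares X with a fixed number. Lowering m can lower X but cannot raise it. This needs no assumption about the true rate or about why reports are missing.

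**3. Illustrative size.** The article gives neither the true symptom rate p nor m. Both are assumptions: p from 10% to 30%, and m of 30, 24 and 18. Loss is taken as unrelated to symptoms, and those without a report contribute no event. With X ~ Binomial(m, p), the chance of meeting the printed success count is P(X ≤ 3):

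| True rate p | m = 30 | m = 24 | m = 18 |
|---|---|---|---|
| 10% | 0.647 | 0.786 | 0.902 |
| 15% | 0.322 | 0.505 | 0.720 |
| 20% | 0.123 | 0.264 | 0.501 |
| 25% | 0.037 | 0.115 | 0.306 |
| 30% | 0.009 | 0.042 | 0.165 |

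If 4 reporters are allowed, P(X ≤ 4) at p = 20% is 0.255, 0.460 and 0.716, so the pattern is the same. On the stop side, P(X ≤ 9) at p = 30%, the chance of avoiding the stop count, is 0.589, 0.847 and 0.979.

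**4. Where count and percentage disagree.**
- Stop: 8 reports among 24 assessed is 8/24 = 33.3%, above the 30% limit. The count 8 lies between 5 and 9 and is scored amend.
- Success: 3 reports among 20 is 15.0%, and among 18 is 16.7%. With 20 to 29 assessed, 3 reports pass on either basis. Changing the denominator alone therefore alters a 3-report success only below 20 assessed.

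**5. Worst case.** With 3 events among 24 assessed, the 6 others could hold 0 to 6 events. The total is 3 to 9 of 30, or 10% to 30%, which runs from the success band to the top of the amend band.

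**The case against.** The strongest reply is that the article never states that a participant without a report is scored symptom-free. A reader might infer such a rule, but it is only the effect of the printed counts. The 15% comes first and the count is in parentheses, so the general available-case statement could be read onto it. The ceilings would then be 4, 3, 3 and 2 for 30, 24, 20 and 18 assessed. At a 20% true rate the chance of success would be 0.255, 0.264, 0.411 and 0.271, with no steady rise as attrition grows. That is a fair reading of the percentage alone. It does not fit the amend and stop counts, which are printed out of 30, and nothing in the text connects the two places.

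A reader might also take the size from the retention bands, 6 lost at the edge of success and 12 at the bottom of the amend band: "amend if 60% to 79% (18-23/30) complete, and stop if less than 60% (<18 participants". The document does not support that. Retention requires both the postintervention and the 1-month assessments, so someone who took the call and attended week 4 but missed the last survey is not retained, yet has been asked about side effects.

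Nor is the criterion limited to home use. It covers simulator sickness and events attributable to device or software generally, so the orientation questionnaire counts as an assessment. To the extent that it captures events, the effect is smaller than the table suggests.

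Finally, the plan has other safeguards: reasons for loss in the flow diagram, an in-person week 4 visit, qualitative signals, and separate retention and adherence criteria. These make the gap visible. They do not change the safety score.

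**Conclusion.** The point holds as a defect in a rule that the article prints, not as missing detail. Safety is the only ceiling among the criteria, its counts are fixed to 30, and no minimum number assessed is set. Missing reports therefore push the result towards success and away from stop.

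The direction is certain under the printed counts. The size is not, because it depends on an assumed symptom rate and an assumed number without a report. If 6 of 30 gave no report and the true rate were 20%, the chance of a safety success would roughly double, from 0.12 to 0.26. The effect would be larger if symptomatic participants were more likely to be lost. The rule should be settled before the counts are known; the article expects the analysis to be complete by April 2026.

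**What to change.** In Progression Criteria:

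1. Apply the existing percentages to participants exposed to the headset, at orientation or at home, who gave at least one side-effect assessment. Count every qualifying event, including those at orientation and dropouts known to be due to adverse events.
2. Report beside it the number exposed but not assessed after home use. Most participants should complete the orientation questionnaire, so the new denominator alone may exclude few of them.
3. Show participants who never used the headset at home under adherence, and keep any orientation event of theirs in the safety count. Restricting the denominator to home users would drop someone made unwell at orientation who never used the headset again.
4. Add a worst-case tabulation that treats exposed participants not assessed after home use as events. If it leaves the success band, do not report safety as an unqualified success.

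The cost is a few sentences and one extra table, using data already being collected. The downside is that success is harder to declare when reports are missing. Under the worst-case count, four unassessed exposed participants already exceed the printed limit of fewer than 4, even with no reported event. The mismatch between that count and 15% of 30 must be reconciled at the same time.

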### Sample Size

Thirty caregivers will be recruited for the study. A cohort of 5 caregiver participants will be recruited from each recruitment site for equal representation, and enrollment will continue until the targeted number is reached. Recruitment sites are Ontario Shores Centre for Mental Health Sciences in Oshawa, Ontario; Baycrest Centre in Toronto, Ontario; Carefirst Community & Senior Services Association, in Toronto, Ontario; London Health Sciences Centre in London, Ontario; and St. Mary’s Hospital in Montreal, Quebec. Recruitment will take place once local ethics clearance has been received from each site’s research ethics board.

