Another strength is the incorporation of both quantitative and qualitative data collection across 3 time points. Quantitative assessments via validated scales (eg, Caregiver Competence Scale, Connor-Davidson Resilience Scale, Empathy Assessment Scale, Perceived Stress Scale) alongside qualitative data obtained from reflection notes, semistructured interviews, and written reflections are expected to yield nuanced insights into outcomes and users’ learning experiences and acceptance of the VR-based intervention.

The findings from this pilot study will provide foundational evidence for the acceptability and feasibility of immersive, simulation–based psychoeducation delivered via VR for family caregivers or care partners of people living with dementia. Should the VR-SIM Carers intervention demonstrate positive outcomes in reducing caregiver stress and improving resilience, empathy, and caregiving competence, future research will focus on large-scale, multisite randomized controlled trials to confirm efficacy and generalizability across diverse caregiver populations and care settings [16]. Further investigation is warranted to identify which caregiver subgroups benefit most, optimal frequency and duration of VR-based interventions, and ways to integrate such technology into existing community and health system supports.

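### Progression criteria: the acceptability and safety bands overlap or leave gaps, data completeness has no stop range, and the overall rule can read as proceed and stop at once, with no stated precedence

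*Protocol article*

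**What the plan says.** All of this is in Methods, Progression Criteria. The denominator comes from Sample Size: "Thirty caregivers will be recruited for the study".

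- **Acceptability:** "Acceptability success is 70% or higher (≥21/30 participants) reporting willingness to use the MVP again or recommend it, amend if 50% to 69% (15-21/30"; stop is below 15/30.
- **Safety, success:** "Safety or tolerability success is 15% or lower (<4 participants) reporting moderate or severe simulator sickness" (or adverse events attributed to the device or software), with no serious adverse event.
- **Safety, amend:** 16% to 30%, where "5-9/30) report moderate symptoms that are remediable".
- **Safety, stop:** "stop if more than 30% (>9 out of 30 participants) report moderate or severe symptoms or any serious adverse event attributable to the intervention".
- **Data completeness:** success is at least 27/30 at baseline and at least 24/30 at each follow-up. Amend is 75-89% (at least 23/30) at baseline or 18-23/30 at a follow-up. No stop range is printed.
- **Overall rule, first branch:** "proceed to a definitive trial without substantive changes if most key criteria meet success thresholds".
- **Overall rule, second branch:** go on with modifications when criteria lie in the amend range and there is no major safety signal.
- **Overall rule, third branch:** "stop and redesign if multiple key criteria fall in the stop range", or if the qualitative data show fundamental problems.

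The section calls the criteria prespecified, says that they guide the decision, and promises that decisions will be reported and justified.

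**The concern.** Feasibility is the pilot's primary focus, and whether to go on to a definitive trial is its main conclusion. A prespecified rule should send each result to one band and each set of bands to one decision. Here some counts fall in two bands or in none, and some sets of bands satisfy two branches of the overall rule. In those cases the choice would be made after the data are seen. The safety criterion matters most: its own text says stop, while the overall rule, read literally, can return the branch that goes forward unchanged.

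**Working it through.** **1. Bands at N = 30.** Each count k from 0 to 30 was placed by the printed counts and again by the printed percentages, using 100 × k/30.

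| Criterion | Overlap by count | Gap by count | Agreement with percentages |
|---|---|---|---|
| Recruitment | none | none | full |
| Retention | none | none | full |
| Adherence | none | none | full |
| Acceptability | 21 (success and amend) | none | differs at 21: 70.0% is success only |
| Safety | none | 4 | differs at 4: 13.3% is success |
| Completeness, baseline | none | 0-22 | agrees where a band is given |
| Completeness, follow-up | none | 0-17 | agrees where a band is given |

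- Retention success is printed only as a percentage: 80% of 30 = 24.
- Acceptability: 20/30 = 66.7% and 21/30 = 70.0%, so 50-69% corresponds to 15-20.
- Safety: 4/30 = 13.3% is within 15% or lower, but 4 is not below 4 and is less than 5. The next count, 5/30 = 16.7%, is in amend.
- Safety, severity: success and stop count moderate or severe symptoms; amend covers only moderate, remediable ones. With 5 to 9 affected, some of them severely or non-remediably, success fails (above 15%), amend does not apply, and stop is not reached unless there is an attributable serious adverse event.

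**2. Overall rule.** Assumptions: six key criteria, most means more than 3 of 6, multiple means at least 2. Five criteria have three states and completeness has two, so there are 3^5 × 2 = 486 patterns.

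*Proceed and stop both met.* This needs 4 successes and 2 stops. Completeness cannot be in stop, so it must be a success, and the two stops come from the other five criteria: C(5,2) = 10 patterns. Not all can occur:
- The Abstract and Results report 21 enrolled by December 2025, so recruitment cannot be below 15. This removes 4 and leaves 6.
- Completeness success means at least 24/30 at each follow-up. If complete measures imply a completed assessment, at least 24 + 24 − 30 = 18 completed both, and the retention stop is below 18. This removes 3 more.
- Three remain: the pairs among adherence, safety and acceptability. One example is safety and acceptability in stop with the other four in success.

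*Safety the only stop, proceed met.* Five successes plus the safety stop (1 pattern), or four successes, one amend and the safety stop (5 patterns), gives 6. Recruitment in amend (at most 23 enrolled) cannot coexist with baseline completeness of at least 27/30, so 5 remain. In each, one stop is not multiple and four or five successes are most, so the overall rule reads as proceed while the safety criterion reads as stop.

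**3. Chance of landing on the two affected counts.** The documents give no expected rates, so these are assumptions, for 30 evaluable participants, with P(X = k) = C(30,k) p^k (1−p)^(30−k).

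| True acceptability | 60% | 70% | 80% | 90% |
|---|---|---|---|---|
| P(X = 21) | 8.2% | 15.7% | 6.8% | 0.2% |

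| True symptom rate | 2% | 5% | 10% | 15% | 20% | 25% |
|---|---|---|---|---|---|---|
| P(X = 4) | 0.3% | 4.5% | 17.7% | 20.3% | 13.3% | 6.0% |

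The peaks are 15.7% at a true rate of 70% and 21.0% at 13.3%, where the assumed rate equals the observed proportion.

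**The case against.** The best reply is that these are slips beside usable percentages: by percentage, 21/30 is success and so is 4/30. The criteria guide rather than bind, they are read with qualitative findings, and every decision will be justified in print. The safety criterion carries its own stop wording, and most and multiple are undefined, so the conflict depends on how they are read.

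Part of this stands. The acceptability slip is a one-digit correction, and three of the six criteria are clean. The completeness gap is partly covered, because fewer than 18/30 assessed at either follow-up already puts retention in stop; low baseline completeness and item-level missing data remain unclassified. But the percentages do not place severe symptoms in 5 to 9 participants, and they do not order the branches of the overall rule. Justifying a choice afterwards does not prespecify it.

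Four stronger readings are tempting and go beyond the documents:
- A reader might infer that 21/30 on acceptability means both proceed and stop. It means success and amend; the proceed/stop conflict comes only from the overall rule.
- A reader might infer that the plan intends safety to be outvoted. The text shows only that precedence is not stated: the condition about major safety signals is attached to the modify branch alone, while the safety criterion says stop.
- A reader might call the affected counts likely. That holds only for assumed rates near the cut-offs.
- A reader might take the Discussion sentence beginning "Should the VR-SIM Carers intervention demonstrate positive outcomes in reducing caregiver stress and improving resilience, empathy, and caregiving competence" as a second trigger for the next trial. It is a remark on future research under Principal Results, not a progression rule, and the article treats caregiver outcomes as exploratory.

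**Conclusion.** The point holds for acceptability, safety, data completeness and the overall rule, and not for recruitment, retention or adherence. At N = 30 one acceptability count has two bands, one safety count has none, severe or non-remediable symptoms in 5 to 9 participants have none, and completeness below its amend limits has none. About 3 feasible patterns satisfy both proceed and stop, and in about 5 more a lone safety stop meets the proceed branch. The full enumeration gives 10 and 6, but those totals include results that can no longer occur or that exclude each other.

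This rests on six criteria, most as more than three, multiple as at least two, the printed denominator of 30, and complete measures implying a completed assessment. The chance of hitting a single affected count runs from about 0.2% to 16% for 21/30 (true rates 60-90%) and about 0.3% to 21% for 4/30 (true rates 2-25%), so no claim about likelihood is made. It should be corrected because the decision to progress is the pilot's main conclusion.

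**What to change.** Before the data are analysed (analysis is due to be complete by April 2026):

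1. Change the acceptability amend count to 15-20/30, as the stated 50-69% requires.
2. Reconcile the safety percentages, counts and severity wording so that every result, including 4/30 and severe or non-remediable symptoms in 5 to 9 participants, falls in exactly one band. Where the limits lie is for the investigators; none is proposed here.
3. State the stop range for data completeness at baseline and at follow-up.
4. Define most and multiple, make the overall branches mutually exclusive, and state a precedence that reconciles the safety criterion's own stop with the most-criteria wording. A rule that any stop-range result blocks going forward unchanged would be one design choice; the text does not require it.

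The cost is wording only. Slightly fewer result patterns may lead to the unchanged-proceed branch.
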